### 2.4. Participants

This study will be carried out in Caceres (Extremadura, Spain), and the participants will be women who have suffered from IPV. For the participants’ recruitment, information leaflets will be developed and distributed among different social resources for IPV victims in the Community of Extremadura. For this purpose, social workers from different IPV victim care resources and people belonging to associations with direct contact with victims will invite the participants on a completely voluntary basis. The participants will be asked for a contact form (email or a telephone number created for this purpose) so that the psychologist of the project can get in touch with them to carry out the evaluation and for eligibility criteria verification. All participants will provide a signed informed consent form agreeing to participate in the study.

Participants will have to meet the following inclusion criteria: (1) to be a woman; (2) over 18 years of age; (3) have suffered IPV, and (4) to be residents in Extremadura. The exclusion criteria include (1) comorbidity with other psychological diseases such as severe mental disorder (schizophrenia or bipolar disorders), personality or eating disorders such as anorexia or bulimia, as these psychological problems require interventions more specific to their nature; (2) participants with comorbidity of physical problems that prevent them from carrying out adventure activities in nature and (3) participants who cannot speak the Spanish language enough to hold a conversation.

### 2.5. Intervention

EG: A multicomponent cognitive-behavioural four-week program (one session per week) will be carried out. This program will be developed over four weekends and will consist of outings to the Jerte Valley for participation both in therapeutic tourism through adventure physical activities and psychological therapy, so every session will be divided into two parts: the psychological component with a one-hour session of group therapy on different psychological and social aspects, conducted by clinical psychologists specializing in IPV and will prepare the women for the adventure activity; and a second part which will consist of different adventure activities, conducted by sport sciences professionals, with an approximate duration of three hours (Figure 1). If necessary, children may accompany their mothers during the intervention. These will be cared for by specialized monitors so that their mothers can carry out the planned activities.

CG: will continue with their usual care.

### 2.6. Measures and Instruments

Various instruments will be used to assess the feasibility and effectiveness of the multi-component program. Evaluation will be carried out in both EG and CG at baseline and post-intervention.

Self-reported psychological assessment will include the following instruments in a paper format booklet:-Brief socio-demographic data sheet: this will include questions related to age, gender, educational level and socio-economic status, etc., and gender-based violence history (questions to assess lived experiences of gender-based violence).-Baessler and Schwarzer’s General Self-Efficacy Scale [32]. It aims to assess a stable sense of personal competence to deal effectively with multiple stressful situations. This questionnaire is composed of 10 items with a 4-point Likert-type response.-Rosenberg Self-Esteem Scale [33]. The scale assesses feelings of self-respect and self-acceptance. The scale includes ten items, half of which are stated positively and half negatively. The items are answered on a 4-point Likert scale (1 = strongly agree, 2 = agree, 3 = disagree, 4 = strongly disagree), and the total score ranges from 10 to 40. Participants will complete the Spanish version adapted by Morejón, et al. [34] (α= 0.72 to 0.88).-Body Shape Questionnaire (BSQ) [35]. This questionnaire assesses the presence of concern and dissatisfaction with body image. It measures dissatisfaction with one’s own body, fear of gaining weight, low self-concept about physical appearance, and desire to lose weight. It consists of 34 items including 4 subscales (body dissatisfaction, fear of gaining weight, low esteem related to appearance, and desire to lose weight) which are measured on a 6-point scale, ranging from “never” to “always”. The total score ranges from 34 to 204, with higher scores showing greater body dissatisfaction. The Spanish validation of Raich, et al. [36], will be completed by participants (α = 0.95 to 0.97) [36].-Beck Depression Inventory, Second Edition (BDI-II) [37]. This is a questionnaire that assesses the presence and severity of depression in adolescents and adults. This consists of 21 items from different areas such as sadness, loss of pleasure, suicidal ideation, etc. Scores range from 0 to 63, including different cut-off points to classify patients according to the following subgroups: normal to minimal depression (0 to 13), mild depression (20 to 28), moderate depression (20 to 28), and severe depression (scores above 29) (α = 0.83) [38].-Perceived Stress Test (PSS) [39]. The PSS assesses the perception of control over environmental demands. It is a self-report instrument consisting of 14 items with a five-point scale response format (0 = never, 1 = hardly ever, 2 = occasionally, 3 = often, 4 = very often). A higher total score obtained is an indication of a higher level of perceived stress (α = 0.82 to 0.81) [40].-EQ-5D-5L. The EQ-5D-5L [41] is a questionnaire that aims to assess health-related quality of life (HRQoL). It is composed of 5 dimensions (mobility, self-care, usual activities, pain or discomfort, and anxiety or depression), with five possible response levels. Health states can be described by a 5-digit number, where the first number is the response to the first question, the second number is the response to the second question, and the third number is the response to the third question. is the answer to the first question, the second number is the answer to the second question, and so on. Given Since the EQ-5D is a preference-based questionnaire, these health states can be converted into a utility index by applying the appropriate formula. This instrument also includes a Visual Analogue Scale (VAS) with a range from 0 (worst imaginable health state) to 100 (best imaginable health state). (best imaginable health state).-Physiological measures will include glucocorticoids, cortisol, and dehydroepiandrosterone (DHEA) analysis through saliva samples. The participants will provide a minimum of 0.5 mL of saliva in a plastic tube recipient Salitubes SLV-4157 (DRG Instruments GmbH, Marburg, Germany) specifically to be used with DRG Salivary Cortisol/DHEA ELISA Kits (DRG Instruments GmbH, Marburg, Germany) twice a day (between 8 and 9 AM for DHEA and cortisol, and between 8 and 9 PM for evening cortisol). All samples will be triplicated to ensure process reliability. Participants will be instructed to collect samples in their homes. Saliva samples will be frozen in women’s freezers and will be brought to the Department of Anatomy of the University of Extremadura medicine Faculty in a mobile freezer, where they were being kept frozen at 21 °C previously to be analysed following the protocol indicated in the kits.

### 2.7. Cost-Effectiveness Analysis

A cost-effectiveness analysis will be conducted with a health system perspective in line with the methodological recommendations of health economists [42], and the guidelines defined in the scientific literature [43]. The study will be conducted considering the costs and health effects of the intervention. Only the direct costs of the program will be considered. Direct costs include medication, primary care visits, and hospital admissions. The salaries of the staff hired under the project will also be considered. It also will include the material costs necessary for the combined intervention.

The average costs and effectiveness, i.e., Quality Adjusted Life Years (QALYs) gained, will be calculated for each group. Subsequently, the incremental cost-effectiveness ratio will be calculated [44], and various sensitivity analyses will be performed, including probabilistic analysis, which will be carried out with 1000 replicates [45]. These replicates will be included in the cost-effectiveness plane and will be used to make the acceptability curve. After doing this we will be able to see in which quadrant of the cost-effectiveness plane the program falls, which will indicate whether the intervention has been more or less costly and effective than the one carried out by the CG.

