### 2.2. Sample Size

Assuming a dropout rate, and accepting an alpha risk of 0.05 and a beta risk of 0.2 in a two-sided test, 11 subjects should be necessary for the intervention and 11 in the control group to recognize, as statistically significant, a difference greater than or equal to 0.18 units [28]. The common standard deviation was assumed to be 0.15 [29], and the correlation coefficient between the initial and final measurement, was 0.6 [30].

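### Section 2.7 builds the ICER from group-average QALYs with no baseline-utility adjustment stated; regressing on the baseline EQ-5D-5L utility would be more precise, by an amount that depends on what QALYs gained means

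*Protocol article*

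**What the plan says.** Section 2.7 states that "The average costs and effectiveness, i.e., Quality Adjusted Life Years (QALYs) gained, will be calculated for each group". The ICER follows from these, then sensitivity analyses that include a "probabilistic analysis, which will be carried out with 1000 replicates". The replicates feed the cost-effectiveness plane and the acceptability curve, and the quadrant of the plane is to be read as the result.

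Utility comes from the EQ-5D-5L. Section 2.6 says that "these health states can be converted into a utility index by applying the appropriate formula", and it schedules the instrument at baseline and after the intervention only. Section 2.2 gives the size as "11 subjects should be necessary for the intervention and 11 in the control group". Section 2.3 describes a simple 1:1 randomisation sequence and states no stratification. Section 2.8 assesses intervention effects by repeated measures ANCOVA adjusted for age and baseline, but does not link that model to the QALY comparison.

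The article does not say how a QALY is built from the two utilities, whether the gain is a total or a change from the woman's own baseline, or whether the group difference is adjusted.

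**The concern.** The steps described in section 2.7 go from group averages straight to the ICER, with no covariate step. If each woman's QALY is the area under her two utilities, half its weight is her utility before treatment, which the programme cannot affect. Any chance difference between arms at baseline then enters the incremental QALY directly, and with 11 per arm such differences are common.

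Over one month the incremental QALY is very small whatever the effect, so its sign, and therefore the quadrant, is easily changed. Replicating an unadjusted difference would show wide uncertainty, but the replicates would still be centred on the imbalanced estimate. The stakes are real because section 4 makes the recommendation conditional on cost-effectiveness.

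**Working it through.** **Inputs from the protocol.** 11 women per arm (2.2); two utility measurements (2.6); an intervention phase of one month (2.1), so T = 1/12 year.

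**The plan's own figure.** Section 2.2 works with "accepting an alpha risk of 0.05 and a beta risk of 0.2 in a two-sided test", "a difference greater than or equal to 0.18 units", and says "The common standard deviation was assumed to be 0.15" and "the correlation coefficient between the initial and final measurement, was 0.6". The normal-approximation formula for two means gives n = 2 × (1.960 + 0.842)² × 0.15²/0.18² = 10.9, so 11 per group, using neither the correlation nor any dropout. With the change-score SD, 0.15 × √(2 × 0.4) = 0.134, n = 8.72, so 9 before dropout. The stated size is therefore reproducible. The outcome behind these inputs is not named, so applying them to utility is an assumption.

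**Further assumptions.** Correlation r = 0.6 for utility (range 0.4–0.8); utility SD s = 0.15–0.25, equal at both visits; true utility gain 0.05–0.18; linear change between visits; no missing data.

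**Formulas.** Let U0 and U1 be baseline and final utility. The standard error of the incremental QALY is (T/2) × s × √(2/11) × f, where:

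- total area under the curve, (U0 + U1)/2 × T, unadjusted: f² = 2 + 2r
- gain from own baseline, (U1 − U0)/2 × T, unadjusted: f² = 2(1 − r)
- regression on U0: f² = 1 − r²

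The two QALY definitions differ only by U0 × T. Once U0 is in the regression, both give the same group coefficient. In all three cases the true increment is T/2 times the true utility gain.

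**Variance ratios (independent of s).**

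| r | Total QALY vs regression, 2/(1 − r) | Share of total-QALY variance due to baseline imbalance, (1 + r)/2 | Gain from baseline vs regression, 2/(1 + r) |
|---|---|---|---|
| 0.4 | 3.3 | 70% | 1.43 |
| 0.6 | 5.0 | 80% | 1.25 |
| 0.8 | 10 | 90% | 1.11 |

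At r = 0.6 the standard-error ratios are √5 = 2.24 and √1.25 = 1.12.

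**Size of chance imbalance.** The standard error of the baseline difference is √(2/11) = 0.43 SD. A difference above 0.5 SD in either direction has probability 24%.

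**Effect of a one-SE imbalance, s = 0.15, r = 0.6.** The imbalance is 0.426 × 0.15 = 0.064.

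- Total QALY: the shift is (1/24) × 1.6 × 0.064 = 0.0043 QALY. A true utility gain of 0.18 is worth 0.18/24 = 0.0075 QALY, so the shift is 57% of it.
- Gain from baseline: the shift is (1/24) × (−0.4) × 0.064 = −0.0011 QALY, smaller and in the opposite direction.

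**Chance of a wrong-signed increment, r = 0.6.**

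| s | True utility gain | Total, unadjusted | Gain from baseline, unadjusted | Regression |
|---|---|---|---|---|
| 0.15 | 0.18 | 5.8% | 0.08% | 0.02% |
| 0.20 | 0.05 | 37% | 26% | 23% |
| 0.20 | 0.10 | 26% | 9.5% | 7% |
| 0.20 | 0.18 | 12% | 1% | 0.4% |

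At s = 0.20 the standard errors are 0.0064, 0.0032 and 0.0028. Simulation of 100,000 trials per setting agrees, except that estimating the slope in 22 women costs regression a little: its standard error is 0.0029, and its wrong-sign chance at a gain of 0.10 is 8%.

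**The case against.** A reader might infer that the plan prescribes a raw comparison of total QALYs and that baseline imbalance will dominate the ICER. The documents do not support that. Section 2.7 uses neither the word raw nor unadjusted and never mentions area under the curve. Reporting averages by group does not exclude an adjusted increment. The word gained can fairly mean change from own baseline, and on that reading most of the imbalance is already removed: at r = 0.6, regression lowers the variance by only a further 20% (1 − 1/1.25). Nor is any of this bias, since randomisation keeps the unadjusted difference correct on average; the issue is precision.

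Three further objections have weight. The article condenses a fuller plan, and section 2.7 cites methodological guidance that is not shown. Section 2.8 does not limit its adjusted analysis to particular outcomes, so it may cover EQ-5D-5L utility as an outcome. The SD, correlation and difference used above come from a calculation whose outcome is unnamed.

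These points lower the size of the concern and make it conditional. They do not remove it. As described, the route to the ICER contains no covariate step, the utility model in 2.8 is not tied to the QALYs, and regression on baseline has the lower large-sample variance on either reading.

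**Conclusion.** The point holds in conditional form. Section 2.7 derives the ICER from group-average QALYs with no baseline-utility adjustment stated, unlike the analysis in section 2.8. Following it as written gives a less precise incremental QALY than the data allow. The loss is large (5-fold in variance) if total QALYs are averaged and modest (25%) if the gain is taken from own baseline; the article does not say which applies. The ratios rest on r = 0.6 for utility, equal SDs at both visits and linear change between them. The wrong-sign probabilities also depend on the assumed SD and true gain and are illustrative only.

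**What to change.** In section 2.7, define each woman's QALY as the area under her two EQ-5D-5L utilities over the follow-up. Estimate the incremental QALY by regressing it on group and baseline utility. Age may be added to match section 2.8, but the argument does not depend on it. Refit the regression in each of the 1000 replicates, and base the ICER, the plane and the acceptability curve on the adjusted increments.

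The cost is a few lines of plan text and analysis code. Baseline utility is already collected, so no new data are needed.

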### 2.8. Statistical Analysis

All data and analyses will be collected and analysed with the SPSS statistical package (version 26.0; SPSS, Inc., Chicago, IL, USA). The Shapiro-Wilk test will be performed to check data normality and to choose between parametric or non-parametric statistical analyses. Continuous socio-demographic variables will be presented as mean (SD) or median (IR) where appropriate, while categorical variables will be presented as proportions. Differences between groups at baseline will be analysed using independent samples t-tests. To assess the effects of the program, two types of analyses will be conducted. Intervention effects will be assessed using a repeated measures ANCOVA test, adjusted for age and baseline values. Cohen’s d (with a 95% confidence interval) will be also included in the results as the effect size. Effect size thresholds will be interpreted as follow: >0.2, small; >0.5, moderate; >0.8, large [46]. Statistical significance will be computed for the effect of time and the interaction group × time. The alpha level will be fixed at *p* ≤ 0.05.

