## 2. Materials and Methods

### 2.1. Study Design and Ethical Considerations

A parallel-group randomized controlled trial will be conducted including a one-month intervention phase. Both for the control group (CG) and experimental group (EG), evaluations will be carried out before the start of the intervention (initial assessment), as well as at the end of the intervention (final assessment). The study will be carried out according to the Consolidated Standards of Reporting Trials Statement (CONSORT) methodology for randomized controlled trials [27].

The Ethics Committee of the University of Extremadura University approved this project (approval code: 45/2022), which will follow the Declaration of Helsinki and their actualizations as amended by the 64th General Assembly of the World Medical Association (Fortaleza, Brazil, 2013) and the Biomedical Research Act 14/2007. Moreover, this study has been registered with the International Standard Randomised Controlled Trial Number (registration number: ISRCTN93835057; https://www.isrctn.com/) (accessed 26 October 2022).

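### The planned significance test of time, adjusted for baseline with only two assessments, does not hold its 5% level and does not compare the arms; group × time is sound and should be named as the treatment effect

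*Protocol article*

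**What the plan says.** Section 2.6 fixes two occasions: "Evaluation will be carried out in both EG and CG at baseline and post-intervention". Section 2.1 says the same.

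Section 2.8 introduces the efficacy analysis with "To assess the effects of the program, two types of analyses will be conducted". The model is "Intervention effects will be assessed using a repeated measures ANCOVA test, adjusted for age and baseline values". After a passage on Cohen's d and its thresholds comes "Statistical significance will be computed for the effect of time and the interaction group × time", with alpha set at 0.05. The section does not say which of the two terms is the treatment comparison, or how age and baseline are coded.

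Section 2.2 supplies the design figures used below: 11 women per arm, a correlation of 0.6 between initial and final measurements, "a difference greater than or equal to 0.18 units" as the target difference, and "The common standard deviation was assumed to be 0.15".

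**The concern.** With two occasions, a time factor exists only if baseline is one of its levels. Entering baseline as a covariate as well makes it both outcome and predictor. That is harmless for one of the two planned tests and harmful for the other.

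Two separate problems affect the time term. First, its p-value does not have the stated error rate. Second, even a correct test of time asks whether women changed on average, controls included. Controls continue usual care (2.5) and may change for reasons unrelated to the programme. In a 22-woman trial with many outcomes, an unranked pair of p-values in the section on programme effects leaves room for a time effect to be reported as if it bore on the programme.

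**Working it through.** **Inputs from the protocol.** Two occasions; 11 per arm, N = 22; r = 0.6; SD 0.15; difference 0.18; two-sided alpha 0.05.

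**Assumed inputs, not in the protocol.** Baseline means and SDs of the scales, and age (40 or 42 years, SD 10).

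**The plan's own figure.** 2 × [0.15 × (1.960 + 0.842) / 0.18]² = 10.90, so 11 per arm. This reproduces without the correlation or any dropout. The sample size is not at issue here; it only fixes N.

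**Step 1: what the model reduces to.** With two occasions, the within-subject part is a regression of the change:

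final − initial = a + b·group + c·age + d·initial + error, with 22 − 4 = 18 residual df.

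The time test is the test of a. The group × time test is the test of b.

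**Step 2: group × time.** Moving the initial score to the right-hand side changes d to d + 1 and leaves a, b, c and the residuals as they were. So b, its standard error and its p-value are those of an ANCOVA of the final score on group, age and baseline. In simulation the two t statistics differed by at most about 3 × 10⁻¹³. Null rejection was 4.9–5.3%, and power at 0.18 was about 88% with 11 completers per arm.

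**Step 3: time, covariates centred at the sample means.** Here a is the mean change over both arms. In units of the outcome variance:
- true variance of a change: 2(1 − 0.6) = 0.80
- residual variance used by the model: 1 − 0.6² = 0.64

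The standard error is too small by a factor √(0.80/0.64) = 1.118. The critical value for 18 df, 2.101, therefore acts as 2.101/1.118 = 1.879, and P(|t₁₈| > 1.879) = 7.7%. Simulation gives 7–8%. Without the baseline covariate the rate is about 5%.

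**Step 4: time, covariates uncentred.** Now a is the expected change at age 0 and baseline score 0. Regression to the mean gives it the value (1 − 0.6) × baseline mean + true change. With no true change and age 40 (SD 10):

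| Assumed baseline | Expected a | Time test rejects |
|---|---|---|
| BDI-II 25, SD 10 | 0.4 × 25 = +10 | 18% |
| PSS 28, SD 8 | 0.4 × 28 = +11.2 | 28% |
| EQ-5D utility 0.70, SD 0.15 | 0.4 × 0.70 = +0.28 | 33% |
| Rosenberg 30, SD 5 | 0.4 × 30 = +12 | 40% |

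These rates come from 3,000 trials each; repeat runs agree to within about two percentage points. Other assumed baselines (2 to 6.7 SD above zero, age 42) gave 14–41%. If BDI-II truly falls by 5 points, the expected a is +10 − 5 = +5, which has the wrong sign. On two of the scales a zero score is not even possible: Rosenberg runs from 10 to 40 and the BSQ from 34 to 204 (2.6).

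**Step 5: no contrast between arms.** Let both arms change equally by 0.09 (0.6 SD; assumed baseline 0.5, SD 0.15), with no programme effect. The time test rejects in 44% of trials uncentred, 89% centred and 85% with no covariates. Group × time stays at 5.1%. The 85% shows that this problem would remain even if the baseline adjustment were removed.

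**The case against.** The strongest reply is that the treatment comparison is already planned and valid. That stands. A reader might infer that the repeated measures ANCOVA as a whole is invalid; Step 2 shows it is not, and the repair leaves the treatment p-value untouched.

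A reader might also infer that the protocol declares the time effect to be an intervention effect. It does not. The sentence on time and group × time comes after the text on Cohen's d and may only list model output to be reported. What can be said is narrower: both terms are named for significance testing where programme effects are assessed, and neither is ranked.

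Thirdly, the 18–40% rates should not be taken as the error rate this trial will have. They require uncentred covariates, which the protocol neither states nor excludes, and they move with assumed means, SDs and ages. Coding may be settled in an analysis plan not shown. The centred figure of 7–8% needs only the protocol's r and N, and it is modest.

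Finally, it is tempting to say the artefact would pass as improvement. That depends on the scale. An upward shift looks favourable on the EQ-5D utility index but unfavourable on BDI-II and PSS, where higher scores are worse.

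None of this rescues the time test. No coding of the covariates makes it a comparison between arms, and centring does not bring it back to 5%.

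**Conclusion.** The point holds for the time term only. As written, its significance test runs at about 7–8% with centred covariates. Uncentred, it runs at about 18–40%, conditional on the assumed baselines and ages, and the estimate can point the wrong way, favourably or unfavourably according to the scale. In both forms it pools the arms, so no result on it can show a programme effect. The calculations rest on normal outcomes, r = 0.6 and 11 completers per arm. Because the valid group × time test is also planned and is unaffected, this should be fixed before analysis but does not undermine the trial's treatment comparison.

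**What to change.** In section 2.8, replace the model sentence and the sentence on time and group × time with wording such as: *For each outcome, the intervention effect is the adjusted experimental minus control difference in the final score, from an ANCOVA of the final score on group, baseline score and age, with its 95% confidence interval. This is equivalent to the group × time test. Cohen's d is derived from this adjusted difference. Change within each arm is described without significance tests.*

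The cost is a wording change. No data collection changes, and the treatment p-value and power are the same as under the present group × time test. All that is given up is the p-value for time.
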